### I (intervention)

All patients will receive anthropometric measurements (BMI, waist circumference, hip circumference), blood-based biochemical analyses (alanine aminotransferase ALT, aspertate aminotransferase AST, γ-glutamine transferase γ-GTP, total cholesterol Tc, triglyceride, high-density lipoprotein cholesterol HDL-c, low-density lipoprotein cholesterol LDL-c), ultrasonic examination (B-mode US, CAP, TAI, TSI) and magnetic resonance imaging proton density fat fraction (MRI-PDFF) before and 1, 3, 6, 12 months after bariatric surgery.

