### C (comparison or control)

Our research constitutes a prospective superiority trial, wherein self-control and blind map-reading served as key components. The study was conducted within a single-center and aimed to assess the efficacy of QUS techniques compared to other imaging methods, anthropometric measurements, and laboratory assessments which were designated as control groups.

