### Anthropometric and laboratory assessments

Anthropometric and laboratory evaluations were conducted as part of the study protocol. Trained physicians performed subject interviews to elicit medical history, medication usage, and alcohol consumption habits. Afterward, anthropometric measurements were taken while subjects were attired in lightweight garments and shoeless. These measurements included height, weight, waist circumference (WC), and hip circumference (HC). Body Mass Index (BMI) was then computed using the individual's weight divided by the square of their height (kg/m^2^). Laboratory assessments were evaluated by obtaining serum samples after an overnight fast and were as follows: ALT, AST, γ-GTP, Tc, Triglyceride, HDL-c and LDL-c.

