### Primary endpoint

In this study, the primary endpoint seeks to evaluate the efficacy of QUS techniques assessing hepatic steatosis, utilizing MRI-PDFF as the gold standard, compared to anthropometric measurements, laboratory assessments and other imaging methods before and after bariatric surgery. Success in this endeavor would be measured by the ability of QUS techniques to better evaluate the degree of hepatic steatosis as compared to other methods, thereby providing diagnostic improvement beyond current practice. Such results would signify the feasibility of using QUS techniques for postoperative evaluation of bariatric surgery.

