### Data analysis

The statistical analysis for this study will be performed using the SAS 9.2 software package (SAS Analytics, Marlow, UK) and R (v4.3.1; R Core Team), which is widely available for commercial use. The significance level has been predetermined to be 0.05 for all two-sided tests. The mean and standard deviation will be used to express normally distributed quantitative data.

To compare quantitative data, a paired t-test will be employed. Meanwhile, categorical variables will be analyzed using the chi-squared test. Pearson correlation coefficients will be utilized to evaluate the relationship between QUS parameters and other factors under consideration. Univariable linear regressions of QUS and other methods on MRI-PDFF were conducted to calculate the adjusted linear correlation coefficient (r). Then receiver operating characteristic (ROC) curves of QUS and other methods for the detection of MRI-PDFF ≥5% and ≥10% were plotted. The best cut-off values were defined as the cut-off values corresponding to the maximum Youden indexes.

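### QUS is compared with anthropometric and laboratory values one at a time, which cannot by itself support a claim of improvement on current practice

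*Protocol article*

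**What the plan says.** - **Comparison.** Data analysis: "Univariable linear regressions of QUS and other methods on MRI-PDFF were conducted", to obtain an adjusted linear correlation for each method. ROC "curves of QUS and other methods for the detection of MRI-PDFF ≥5% and ≥10% were plotted". Pearson correlations are also planned. No model that combines routine values is named anywhere in the article.
- **Claim.** Under C (comparison or control): "Our research constitutes a prospective superiority trial". The Primary endpoint section sets QUS, with MRI-PDFF as the reference, "compared to anthropometric measurements, laboratory assessments and other imaging methods before and after bariatric surgery", and describes success as QUS grading steatosis better than the other methods, "thereby providing diagnostic improvement beyond current practice".
- **Data.** Three anthropometric values (BMI, waist and hip circumference) and seven laboratory values ("ALT, AST, γ-GTP, Tc, Triglyceride, HDL-c and LDL-c") are collected, together with B-mode US, CAP, the two QUS parameters and MRI-PDFF. The After inclusion section puts all examinations on the same day.
- **Practice.** The Introduction calls BMI the established postoperative measure, says that changes in laboratory values are also used but lack standardization, and says that B-mode US is in routine clinical use.

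**The concern.** The analysis and the conclusion answer different questions. A univariable comparison asks whether AC-TAI or SC-TSI tracks MRI-PDFF better than, say, LDL-c or hip circumference does alone. The stated conclusion is that QUS improves on what clinicians already have, and for each patient they have all of these values at once. QUS could beat every one of them singly and still add little once they are taken together. The trial could then report an improvement on current practice that its own data, differently analysed, would not bear out. The planned regressions cannot tell the two situations apart.

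**Working it through.** The plan gives no figure for this comparison, so there is none to reproduce. The sample-size figure of 75 rests on sensitivity, specificity and prevalence and does not bear on the point. The checks below show direction, possible size, and what the trial can support.

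**1. Direction.** In the population, the best linear combination of several values never correlates less with MRI-PDFF than its best single member. Taking values singly therefore makes the comparator weaker or leaves it unchanged.

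**2. Possible size.** From the document: adjusted r = 0.632 for AC-TAI with MRI-PDFF (Results, 21 participants). Assumed, because the document gives neither: each routine value correlates r with MRI-PDFF, and the values correlate ρ with one another. For k such values, R = √[k r² / (1 + (k−1)ρ)].

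| k | r | ρ | R² | R |
|---|---|---|---|---|
| 10 | 0.20 | 0.5 | 0.40/5.5 = 0.073 | 0.27 |
| 10 | 0.20 | 0.1 | 0.40/1.9 = 0.211 | 0.46 |
| 10 | 0.30 | 0.5 | 0.90/5.5 = 0.164 | 0.41 |
| 10 | 0.30 | 0.2 | 0.90/2.8 = 0.321 | 0.57 |
| 10 | 0.30 | 0.1 | 0.90/1.9 = 0.474 | 0.69 |
| 4 | 0.35 | 0.3 | 0.49/1.9 = 0.258 | 0.51 |
| 4 | 0.40 | 0.2 | 0.64/1.6 = 0.400 | 0.63 |
| 4 | 0.40 | 0.1 | 0.64/1.3 = 0.492 | 0.70 |

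For the four-value rows, adjusting at n = 75 by √[1 − (1−R²)·74/70] gives 0.46, 0.60 and 0.68. Against 0.632, the routine values together range from far behind to slightly ahead.

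**3. What that does to a test.** The plan names no test between correlations. Using one for two dependent correlations (Dunn–Clark) as an illustration, take N = 100, two-sided 0.05, AC-TAI at 0.632 and a correlation of 0.3 between AC-TAI and the comparator.
- Single value at 0.30: Fisher z values 0.745 and 0.310, difference 0.435, standard error 0.128. The ratio is 3.40, so power is Φ(3.40 − 1.96) ≈ 0.93.
- Combined set at 0.567: Fisher z values 0.745 and 0.643, difference 0.102, standard error 0.135. The ratio is 0.76, so power is Φ(0.76 − 1.96) ≈ 0.11.

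Over the other assumed correlations between AC-TAI and the comparator, the ranges are about 0.89–0.98 and 0.11–0.14. The combined set is treated here as a fixed score, not one fitted in the same data.

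**4. How firm the anchor is.** Treating 0.632 as an ordinary correlation, n = 21 gives 0.745 ± 1.96/√18 = 0.745 ± 0.462 on the Fisher scale, or about 0.28 to 0.84. The pilot group had suspected NAFLD and a mean BMI of 26.43, below the trial's entry limit of 27.5.

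**5. What the trial can support.** At the assumed 80% prevalence, taken as the share with MRI-PDFF ≥5%, patients without steatosis at baseline number 0.20 × 75 = 15 to 0.20 × 100 = 20. At the 95% that the Introduction cites for morbid obesity, there would be about 4 to 5. A logistic model at ≥5% with several routine values plus two QUS parameters would be unstable. A linear model on continuous MRI-PDFF with four routine values, B-mode grade as one score and two QUS parameters has seven slopes, or 75/7 ≈ 11 to 100/7 ≈ 14 patients per slope.

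**The case against.** A reader might infer that superiority over current practice is too easy to claim, or that the plan would declare it on the strength of beating BMI or LDL-c. The documents do not support that reading.

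- B-mode US and CAP are comparators too. If QUS must do better than every listed method, a single laboratory value is not the hardest of them.
- Data analysis states no decision rule and no test between methods. The word univariable attaches to the regressions only; the ROC sentence does not say whether values are combined.
- AC-TAI and SC-TSI are also taken singly, which weakens QUS as well.
- The Introduction describes no combined score as current practice. A regression fitted to this trial's own MRI-PDFF would be a new model, so it is not the only legitimate comparator.
- The article is condensed, and further models may stand in an analysis plan not shown.

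All of this stands, and it limits the point. What remains is that the article fixes the form of the regressions and fixes the wording of the conclusion, and the first cannot deliver the second. Beating CAP or B-mode US would show a better imaging method, not a gain over the routine values taken together.

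**Conclusion.** The point holds in a limited form. One-at-a-time comparison with anthropometric and laboratory values does not show that QUS adds to the routine information the trial itself collects, so it cannot alone carry the current-practice wording. The direction is certain in the population. The size is unknown: it depends on marker correlations that the article does not give, and the plausible range runs from a negligible gap (0.27 combined against 0.20 alone) to one that removes the QUS advantage (0.69 against 0.632). The 0.632 is itself imprecise and comes from a leaner group. The planned comparisons remain valid as head-to-head results; the mismatch lies between them and the conclusion drawn. It deserves correction because the remedy needs only data already planned.

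**What to change.** Keep the univariable and head-to-head results, including those against CAP and B-mode US. Add to Data analysis one pre-specified nested linear model:

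- **Outcome:** continuous baseline MRI-PDFF, one record per patient.
- **Base model:** a short fixed set already collected, for example BMI, waist circumference, triglyceride and ALT, with B-mode grade.
- **Extended model:** the same set plus AC-TAI and SC-TSI together.
- **Report:** the gain in R², corrected for optimism (for example by bootstrap), with a confidence interval.

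Treat any logistic panel at ≥5% as exploratory. In Primary endpoint, allow the current-practice wording only if the added gain is shown; otherwise limit the conclusion to superiority over the individual methods. A baseline model speaks for baseline only; extending the claim to the postoperative visits would need the same comparison there, with within-patient correlation allowed for.

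Cost: a few sentences and a little more analysis, with no new data or visits. The claim becomes harder to reach, and the set must stay short and be fixed before the data are seen.

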## Results

Prior to the fomal study, we recruited 21 Chinese participants who satisfied: (1) age between 18 and 85 years old; (2) with suspected NAFLD, and (3) agreed to receive QUS, and MRI examination. They received ultrasonic examination (TAI, TSI, CAP) and MRI-PDFF (Figure 3).

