**Figure 3 F3:**
[figure not shown]
Quantitative analysis of liver fat in an obese Chinese male. Based on B-mode ultrasound image, the color-coded maps of TAI map (**A**) reflecting center frequency and TSI map (**B**) reflecting Nakagamia parameters are generated. (**C**) MRI-PDFF values were 14.72%.

The average BMI of all participants was 26.43, which meets the diagnostic criteria for overweight. More than 50% of patients (15/21, 71.43%) presented with symptom of right upper abdominal distension. For the value of MRI-PDFF, the average was 13.86%. MRI results from eight patients were below 10%. For MRI-PDFF ≥10%, a total of 13 patients were in this category (13, 62.9%).

All the data were analyzed in R (v4.3.1; R Core Team). A two-sided *P* < 0.05 was considered statistically significant. AC-TAI showed moderate correlations with MRI-PDFF (adjusted *r* = 0.632; *P* < 0.05). Linear correlation between SC-TSI and MRI-PDFF was not significant (*P* = 0.982) (Table 1). For MRI-PDFF ≥10%, SC-TSI showed moderate correlations with MRI-PDFF (adjusted *r* = 0.677; *P* < 0.05) (Figure 4). In a way, the results signified the feasibility of using QUS techniques for postoperative evaluation of bariatric surgery.

**Table 1 T1:** Linear regression between AC-TAI/SC-TSI and other parameters.

Parameters	AC-TAI		SC-TSI	
	Adjusted R	*P*-value	Adjusted R	*P*-value
CAP	0.578	<0.05	0.343	0.070
MRI-PDFF	0.632	<0.05	0.229	0.982

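### The undefined adjusted r planned against MRI-PDFF appears, from the pilot table, to be the root of the absolute value of adjusted R-squared, which misreports near-zero correlations

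*Protocol article*

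**What the plan says.** The Data analysis section of the protocol article names two correlation-type statistics. The first is an ordinary correlation: "Pearson correlation coefficients will be utilized to evaluate the relationship between QUS parameters and other factors under consideration". The second covers the comparison with the reference standard: "Univariable linear regressions of QUS and other methods on MRI-PDFF were conducted to calculate the adjusted linear correlation coefficient (r"). No formula is given for the second. The same section plans ROC curves for QUS and the other methods at MRI-PDFF thresholds of 5% and 10%, and sets the test level: "The significance level has been predetermined to be 0.05 for all two-sided tests".

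The Results section shows the second statistic in use in the pilot: "Prior to the fomal study, we recruited 21 Chinese participants who satisfied" the pilot's entry criteria. Table 1 has columns headed Adjusted R and P-value, first for AC-TAI and then for SC-TSI. Its two rows are "CAP 0.578 <0.05 0.343 0.070" and "MRI-PDFF 0.632 <0.05 0.229 0.982". The text comments: "Linear correlation between SC-TSI and MRI-PDFF was not significant (*P* = 0.982"). It also reports an adjusted r of 0.677 for SC-TSI among the 13 participants with MRI-PDFF of at least 10%.

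**The concern.** With one predictor and a known sample size, the correlation coefficient and its P-value determine each other apart from sign. The pair 0.229 and 0.982 cannot both describe an ordinary correlation in 21 people: one is a weak association, the other almost none. The printed coefficient must therefore be something else, and the plan does not say what.

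This matters because the regression sentence is the one that places QUS and its comparators (anthropometry, laboratory values, other imaging) side by side against MRI-PDFF, and the Primary endpoint section asks whether QUS does better than those comparators. The protocol does not predict the comparators' correlations. For any that are close to zero, a statistic that rises again as the correlation falls to zero would misstate their strength and could misorder them. A root also carries no sign, so an inverse association would print like a positive one.

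**Working it through.** **Inputs.** n = 21, so 19 residual degrees of freedom (Results). Table 1 pairs: SC-TSI/MRI-PDFF 0.229, P = 0.982; SC-TSI/CAP 0.343, P = 0.070; AC-TAI/MRI-PDFF 0.632; AC-TAI/CAP 0.578. Subgroup: 0.677, n = 13. Main study: minimum 75, planned 100 (Sample size).

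**Formulas.** From a two-sided P, take t on n - 2 degrees of freedom; then |r| = t / sqrt(t² + n - 2). Adjusted R² = 1 - (1 - r²)(n - 1)/(n - 2). Candidate for the printed figure: sqrt(|adjusted R²|).

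**Reproducing 0.229.**
- P = 0.982 at n = 21 gives |r| = 0.0052 (0.0051 to 0.0054 over the rounding range of P, 0.9815 to 0.9825).
- Adjusted R² = 1 - (1 - 0.0052²)(20/19) = -0.0526.
- sqrt(0.0526) = 0.229, as printed. This is essentially sqrt(1/19) = 0.2294, the value the formula returns when r = 0.

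**Second entry.** 0.343² = 0.1176; R² = 1 - (1 - 0.1176)(19/20) = 0.162; |r| = 0.402; P = 0.0707, against 0.070 printed. In the other direction, P of 0.0704 to 0.0705 gives 0.343, so the pair agrees, though near the edge of the rounding range.

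**Other readings tried.**

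| Reading | Implied P at n = 21 | Printed P |
|---|---|---|
| 0.229 as plain r | 0.318 | 0.982 |
| 0.229 as root of a positive adjusted R² (r = 0.316) | 0.163 | 0.982 |
| 0.229 as adjusted R² itself | 0.016 | 0.982 |
| 0.343 as plain r | 0.128 | 0.070 |

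With the candidate formula and P = 0.982, n = 19, 20 and 22 would print 0.2425, 0.2356 and 0.2235. Of the sizes tried, only n = 21 fits.

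**Consequence in the main study, if the formula is kept.** For one predictor, adjusted R² = (r²(n - 1) - 1)/(n - 2).
- At r = 0 the printed value is sqrt(1/(n - 2)): 0.117 at n = 75 and 0.101 at n = 100.
- It falls to zero at |r| = sqrt(1/(n - 1)): 0.116 and 0.101.
- It returns to its r = 0 value when r²(n - 1) - 1 = 1, that is |r| = sqrt(2/(n - 1)): 0.164 and 0.142. Below that, a null marker prints higher than a weak one. For example, r = 0.10 prints as 0.060 at n = 75 and 0.010 at n = 100.
- When the true correlation is zero, adjusted R² is negative with probability P(F(1, n - 2) < 1), about 0.68 at both sizes.

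**Larger values.** Where adjusted R² is positive, inverting the formula gives |r| of 0.655 for 0.632 (95% CI 0.31 to 0.85, Fisher z), 0.606 for 0.578, 0.402 for 0.343, and 0.710 for 0.677 at n = 13 (95% CI 0.26 to 0.91).

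**The case against.** The strongest reply concerns scope, since the arithmetic itself is hard to dispute.

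- **The formula is not in the plan.** It is inferred from two table cells, and the regression sentence is in the past tense while the Pearson sentence is in the future, so it might describe only the pilot. The first part stands, and the point must be put as an inference. The tense is weak evidence: the ROC sentence is also in the past tense, and no pilot ROC result is reported.
- **It is not the only scale.** The ROC curves also compare QUS with the other methods against MRI-PDFF and are unaffected. This stands. A reader might infer that the primary comparison is invalid. The documents do not support that, because the Primary endpoint section does not tie success to the adjusted r. The planned Pearson coefficients are less of an answer: they are stated for QUS against other factors and do not clearly cover the comparators against MRI-PDFF.
- **Direction is not necessarily lost.** The regression behind the root has a signed slope, and nothing says it will be withheld. So only the printed coefficient lacks direction.
- **Only weak markers are misordered.** This stands, within the bounds shown in the working. It would touch a conclusion about QUS only if a QUS parameter fell in that range, as SC-TSI did in the whole pilot sample.
- **No stated conclusion uses 0.229.** This also stands. The text says "Linear correlation between SC-TSI and MRI-PDFF was not significant", and neither the text nor the abstract cites the coefficient. A reader might infer that the pilot's headline values of 0.632 and 0.677 are wrong in the same way; they are only shrunk, in the ordinary manner of an adjusted R-squared.

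The word adjusted is not itself a fault: a degrees-of-freedom adjustment is standard even with one predictor.

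**Conclusion.** The concern holds in a bounded form. The SC-TSI against MRI-PDFF entry in Table 1 is wrong as a correlation: its own P-value implies |r| of about 0.005 (95% CI about -0.43 to 0.44), not 0.229. The likeliest explanation is a square root taken of adjusted R-squared after its minus sign was ignored. Two entries fit this and none of the other readings tried does, but it remains an inference. It assumes that all 21 participants contributed to Table 1 and that the printed P-values come from the univariable regressions.

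The Data analysis section names this undefined statistic for QUS and its comparators against MRI-PDFF. If it is computed as in the pilot, near-zero correlations will be misreported, by up to about 0.117 at n = 75 or 0.101 at n = 100. The documents do not support going further and saying that the ROC analyses, the sample size or the moderate pilot correlations are compromised. It should be fixed because it changes reported numbers in the central comparison, but it is not a critical defect.

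**What to change.** In the Data analysis section, replace the adjusted r with the signed Pearson correlation and its 95% confidence interval, for QUS and every comparator against MRI-PDFF, and use Spearman for the four-level B-mode grade. Alternatively, report adjusted R-squared under that name and print negative values as negative.

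Correct Table 1 from the source data. The SC-TSI against MRI-PDFF entry should be |r| of about 0.005; its sign cannot be recovered from the P-value and must come from the investigators' data. Restate the other entries, and the subgroup value, as signed r with confidence intervals.

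The cost is one sentence in the analysis section and one corrected table, plus the matching figures in the text and abstract. No new data are needed.

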**Figure 1 F1:**
[figure not shown]
NAFLD is a progressive disease, ranging from simple steatosis to NASH and cirrhosis. QUS techniques show good diagnostic performance for hepatic steatosis detection in obese individuals. QUS parameters (SC-TSI) show a significant correlation with hepatic steatosis (19, 20).

The protocol is aimed to provide a method to assess hepatic steatosis with QUS techniques (TAI, TSI) in morbidly obese individuals before and after bariatric surgery, and to compare with anthropometric measurements, laboratory assessments and other imaging methods. Thereby, the application value of QUS techniques (TAI, TSI) in quantitatively assessing hepatic steatosis after bariatric surgery will be clarified.

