## Conclusion

In conclusion, this article has described methods for using QUS techniques (TAI, TSI) to assess hepatic steatosis and its changes in obese individuals before and after bariatric surgery. In addition, we compare QUS techniques to anthropometric measurements, laboratory assessments and other imaging methods. By this study, QUS techniques will be signed a widespread availability, real-time functionality, and low cost approach for assessing hepatic steatosis before and after bariatric surgery in obese individuals. Our pre-experiment results signified that using QUS techniques for postoperative evaluation of bariatric surgery is promising. Our study is the first one in China to investigate the application value of QUS techniques (TAI, TSI) in quantitatively assessing hepatic steatosis after bariatric surgery. Our study will provide strong evidence regarding whether obese people can truly benefit from QUS techniques in liver fat quantification.

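### On the continuous scale, accuracy against MRI-PDFF is measured only by correlation, which gives no error in PDFF points and cannot be compared before and after surgery

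*Protocol article*

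**What the plan says.** The end of the Introduction promises that "the application value of QUS techniques (TAI, TSI) in quantitatively assessing hepatic steatosis after bariatric surgery will be clarified". The Conclusion goes further: "Our study will provide strong evidence regarding whether obese people can truly benefit from QUS techniques in liver fat quantification". The Primary endpoint section takes MRI-PDFF as the reference standard and defines success as QUS evaluating the degree of steatosis better than the other methods, before and after surgery.

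For accuracy against MRI-PDFF as a continuous quantity, the Data analysis section offers Pearson coefficients and this: "Univariable linear regressions of QUS and other methods on MRI-PDFF were conducted to calculate the adjusted linear correlation coefficient (r"). The same section plans ROC curves for PDFF ≥5% and ≥10% with maximum-Youden cut-offs, and paired t-tests for quantitative data. It names no measure of error in PDFF points, and no analysis of change in QUS against change in PDFF.

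**The concern.** The claim is about quantification, but the named continuous measure is unitless. Two consequences follow.

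- **No error in PDFF points.** As worded, each method is regressed on MRI-PDFF, so the residual error is in that method's own units (for CAP, dB/m). Only r is carried forward. A moderate and significant r could then be taken as evidence of quantification, whatever the error in PDFF points.
- **Dependence on spread.** r reflects the spread of PDFF among the patients at a visit as well as the error of the method. If surgery narrows that spread, r falls with no loss of measurement quality. A lower post-operative r could then be mistaken for QUS failing after surgery, the setting the trial is about.

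**Working it through.** **Inputs from the article (Results, text below Figure 3, and Table 1).** Pilot n = 21 ("Prior to the fomal study, we recruited 21 Chinese participants who satisfied" the pilot's entry criteria). Adjusted r of AC-TAI with MRI-PDFF = 0.632. On the PDFF distribution: "For the value of MRI-PDFF, the average was 13.86%. MRI results from eight patients were below 10"%. No SD of PDFF is stated, before or after surgery.

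**Step 1. Reading the adjusted r.** Taken as the square root of adjusted R², the unadjusted value is
r = √[1 − (1 − 0.632²) × 19/20] = √0.429 = 0.655.
This reading is supported by another entry in Table 1. For SC-TSI with CAP, an adjusted r of 0.343 at n = 21 gives P = 0.071 on this reading (stated: 0.070), but P = 0.128 if 0.343 is a raw r.

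**Step 2. A plausible PDFF SD (assumption).** Solve for the SD that gives mean 13.86 and P(<10) = 8/21:
- log-normal: σ = 0.560, SD = 13.86 × √(e^0.3135 − 1) = 8.41
- gamma: shape 2.73, SD = 13.86/√2.73 = 8.39
- normal: SD = (10 − 13.86)/(−0.303) = 12.7, which puts part of the distribution below zero PDFF and is set aside.

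I use 8.4 as the central value and 5 to 10 as the range.

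**Step 3. 95% limits for PDFF predicted from QUS** = 1.96 × SD × √(1 − 0.429).

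| Assumed SD | Residual SD | 95% limits (points) |
|---|---|---|
| 5 | 3.8 | ±7.4 |
| 8.4 | 6.3 | ±12.4 |
| 10 | 7.6 | ±14.8 |

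Using 1 − 0.632² in place of 1 − 0.429 gives ±7.6, ±12.8 and ±15.2. At SD 8.4 the limits around 13.9% run from about 1% to 26% and span both ROC cut-offs. At SD 5 the full width of 14.8 points still exceeds the 5-point gap between the cut-offs.

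**Step 4. Effect of a narrower spread.** Suppose QUS is linear in PDFF with constant error. In PDFF units that error SD is 8.4 × √(1/0.429 − 1) = 9.7. Hold it fixed and let r = SD/√(SD² + 9.7²):

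| PDFF SD | r | Slope, PDFF on QUS | 95% limits, PDFF on QUS | Residual SD ÷ slope, QUS on PDFF |
|---|---|---|---|---|
| 8.4 (baseline) | 0.655 | 0.43 | ±12.4 | 9.7 |
| 4 (assumed) | 0.38 | 0.15 | ±7.2 | 9.7 |
| 3 (assumed) | 0.30 | 0.09 | ±5.6 | 9.7 |
| 2 (assumed) | 0.20 | 0.04 | ±3.8 | 9.7 |

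Working instead from r = 0.632 and the ratio u of post- to pre-operative SD, r′ = ru/√(1 − r² + r²u²). This gives 0.52, 0.38 and 0.20 for u = 0.75, 0.5 and 0.25.

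Under this model r falls, and the regression of PDFF on QUS changes its slope and limits, although nothing about QUS has changed. Only the direction the protocol already names, QUS on PDFF, is unaffected by the range.

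**The case against.** Several points on the other side are sound.

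- **The trial is not judged by r alone.** A reader might infer that it is. The Data analysis section also plans ROC curves, the Sample size section uses sensitivity and specificity, and the paired t-tests address pre/post differences. None of these gives accuracy in PDFF points, but the point must be confined to continuous accuracy against MRI-PDFF.
- **Ranking of methods within a visit is unaffected.** The primary comparison is QUS against other methods. At one visit, ranking by r and ranking by residual SD of predicted PDFF agree.
- **The misreading is not written into the plan.** Nothing says that r before surgery will be set against r after, or that a lower r means failure. The endpoint covers both periods, however, and the Results section already takes a correlation in the pilot as a sign of feasibility for post-operative evaluation.
- **A reader might infer that the regression direction is wrong and should be reversed.** Step 4 shows otherwise. A reversed regression with a before/after term could signal a change caused only by the narrower range, and its shrinking limits would make QUS look more accurate after surgery.
- **This is reporting detail.** A fitted regression already yields slope and residual SD, and an article may leave tables to a fuller document. But this article does choose its measure, giving r as the purpose of the regressions, and that measure does not match the claim.

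**Conclusion.** The point holds in this limited form: correlation alone cannot support the quantification claim, and r before and after surgery cannot be compared.

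The size is illustrative. A reader might take ±12 PDFF points as a property of the trial, but the documents do not support that. It needs an SD near 8, which is not stated. The honest range is about ±7 to ±15 for SDs of 5 to 10, at the baseline spread only. The limits also treat a skewed quantity as symmetric with constant variance. The pilot enrolled people with suspected NAFLD and mean BMI 26.43, whereas the trial enrols patients with BMI ≥27.5 scheduled for gastric bypass.

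Nor do the documents establish that r will fall. The drop from about 0.65 to 0.2–0.4 assumes a post-operative SD of 2 to 4 and unchanged QUS error. A narrower spread is plausible, since the Discussion cites a bypass cohort in which steatosis disappeared in 84%, but no post-operative PDFF spread is given.

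**What to change.** In the Data analysis section:

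1. Keep the regression of each continuous method on MRI-PDFF. Report intercept, slope and residual SD at baseline and at 1, 3, 6 and 12 months, with residual SD divided by slope as the error in PDFF points and a confidence interval.
2. Test the before/after difference in this direction, with a model that allows for repeated visits within patient.
3. Relate change in QUS to change in MRI-PDFF.
4. If prediction limits from MRI-PDFF on QUS are also given, report them by visit with that visit's PDFF SD and label them as specific to that range.
5. Keep r as descriptive, shown with the visit's PDFF SD. Base any claim of post-operative quantification on the post-operative error in PDFF points.

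The cost is some extra analysis of measurements already scheduled, with no new visits or patients. Reported accuracy will look less favourable than a moderate correlation. The post-operative estimate may also be imprecise. With 100 patients and the Step 4 assumptions, the relative standard error of the slope is 9.7/(SD × √99): 12% at SD 8.4, 24% at SD 4 and 49% at SD 2. That is a reason to show the interval.
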